### Study setting

This study will be conducted within the vocational rehabilitation services at Tuscaloosa VA Medical Center and the Birmingham VA Health Care System.

### Individual placement and support intervention

IPS is a manualized model of supported employment that focuses on obtaining and maintaining competitive employment that align with the participants’ skills, abilities, knowledge, career interests, and prevocational training [34]. The IPS model encompasses eight principles: (1) *Competitive Employment:* The IPS intervention assists participants to directly engage in a competitive job rather than prevocational training or set-aside sheltered jobs. (*2) Systematic Job Development:* IPS specialists build an employer network based on participant’s interests, developing relationships with local employers by making systematic contacts. (3) *Rapid Job Search:* IPS specialists use a rapid job search approach to help participants obtain employment as soon as possible, rather than providing lengthy pre-employment assessment, training, and counseling. (4) *Integrated Services:* The IPS intervention is closely integrated with the treatment team, in this case the outpatient substance use treatment or MOUD program. (5) *Benefits Counseling:* IPS specialists help veterans obtain personalized, understandable, and accurate information about their VA, Social Security, Medicaid, and other government entitlements. (6) *Zero Exclusion:* IPS embraces the notion of “zero exclusion” criteria, i.e., does not preclude participants because of level of disability, work history, or active substance use. (7) *Time-Unlimited Support*: IPS follow-along vocational supports are continued for as long as the participant wants and needs the support (in this case for 18-months due to the time limits of the study). The unlimited support provides help during job transitions if the first job is not the preferred or best-matched job. (8) *Worker Preferences:* The IPS intervention is based on the participant's preferences and choices rather than the IPS specialist’s or treatment team’s judgements. The caseload size for an IPS Specialist is 20–25 clients. The IPS specialists provides all phases of employment services such as intake, assessment, job development, and job coaching.

### Treatment-as-usual non-*IPS* vocational rehabilitation services

The participants assigned to non-IPS-VR will participate in available VA VR services at the study sites, except for IPS. The non-IPS-VR services may include two types of Compensated Work Therapy (CWT): Transitional Work or Community Based Employment Services. Transitional Work refers to a set-aside, minimum-wage, short-term job, typically in the VA setting. Community-Based Employment Services involves a community job search, placement in a competitive job, with limited follow-along support that typically ends after the veteran begins a new job.

### *IPS* specialist training and fidelity monitoring

The IPS specialists initially attend a 5-week online IPS course provided by the IPS Employment Center [35]. The IPS manual entitled *Supported Employment: Applying the Individual Placement and Support (IPS) Model to Help Clients Compete in the Workforce* [34] and the VHA VR Program Guide are provided to the IPS specialists for training and reference. The IPS trainer/mentor provides technical assistance via weekly teleconferences and intermittent on-site visits throughout the study timeline.

On an annual basis, the IPS fidelity monitor will make an on-site visit and conduct a 2-day fidelity monitoring. Fidelity monitoring involves observing the IPS specialists in the field during job development and interaction with participants, interviews participants, interviews with clinical treatment providers, interviews leadership, and review of the VA electronic medical record. Using the 25-item Supported Employment (SE) Fidelity Scale, the IPS fidelity monitor provides feedback on the fidelity rating to the investigators to aid in working with the IPS specialists to ensure high quality IPS services. The IPS fidelity monitor also evaluates the non-IPS-VR treatment arm using the same methods to ensure that the control arm is rated ≤ 55 on the SE Fidelity Scale (i.e., not supported employment). If non-IPS-VR is rated > 55 on the SE Fidelity Scale (i.e., non-IPS-VR takes on similarities to IPS), the research team will not interfere or modify usual care and will subsequently explore this variable in the analysis. The SE Fidelity Scale is comprehensive, detailed, and research-based [36, 37]. The relationship between IPS fidelity and employment outcomes using the 25-item IPS fidelity scale has been shown to have predictive validity [38].

### Data analyses

Descriptive statistics will summarize the socio-demographic and clinical characteristics of the sample at baseline. Continuous variables will be summarized by means, standard deviations, medians, and ranges. Categorical variables will be summarized by frequencies and rates. Although we expect randomization to produce equivalent groups, we will compare the two groups (IPS vs. non-IPS-VR) on baseline variables, using t-tests for the continuous variables and chi-square tests for categorical variables.

### Primary outcome analysis

The target sample size is 120 randomized participants (60 per study arm). The sample size was based on our most recent IPS study at the Tuscaloosa VA Medical Center that evaluated IPS in the primary care setting as nearly half of the participants had a SUD diagnosis. We expect that more than 84% will complete the intervention as randomized and greater than 95% will provide analyzable employment data. The between-group effect size was 0.55 in favor of IPS in the prior study, for which our projected sample size (54 per group with > 2 months data) would provide > 81% power. Very conservatively assuming that only 90% provide analyzable data this yields approximately 54 participants per group. This provides 80% power to detect a difference in means between groups of 0.54 standard deviations for a continuous outcome. The primary employment outcome is the number of weeks with competitive employment over the 18-month follow-up period. A week scored as “worked” is one in which a competitive job was held for any number of hours or days during that week. A week scored as “not worked” is one in which there was no competitive job held, or there were no employment data (i.e., early exit or missing data). The analysis of the primary outcome will use longitudinal mixed-effects regression models considering the cumulative number of weeks worked at each assessment as the dependent variable and study arm (IPS vs. non-IPS-VR) as the main independent variable adjusted for gender. Study site will be treated as a random effect, as will participant to account for the nesting of participants within sites and the multiple observations per person. We will initially specify the covariance structure of the repeated outcomes as unstructured and will proceed respectively to autoregressive and exchangeable structures if convergence issues are encountered. Prior to final modeling we will examine longitudinal plots of the employment data by group to evaluate whether the most appropriate model and any possible interaction effect appears to be additive (linear regression) or multiplicative (suggesting negative binomial regression), whether time should be included as categorical or linear, and whether it appears that a group*time interaction term is required to faithfully model the data.

The primary hypothesis that participants randomized to IPS will work more weeks over the 18-months compared to those randomized to non-IPS-VR will be evaluated using predicted marginal means (i.e., LS-means) to estimate the difference in hours worked and test significance at the *p* < 0.05 level. Adhering to the principle of intent-to-treat, participants may discontinue the treatment intervention, but will be encouraged to remain in the study for outcome assessments for the 18-month follow-up period and will be analyzed as-randomized.

The exploratory employment outcome is the dichotomous classification of whether each participant is a ‘steady worker’ operationalized as a participant who holds a competitive job for at least 50% of the 18-month follow-up period. The analysis for this outcome will follow the same structure as for the primary employment outcome but using logistic rather than linear regression. Similar analyses for overall intervention effects will also consider outcomes of total time worked (days and hours), income earned from competitive sources, and the type and number of jobs held. These analyses will be descriptive and will be used to identify the overall time-trends of employment between the groups, including when the highest probability of employment is reached and whether the efficacy appears to decline after a period of time. This information can be used to further refine future IPS interventions to maximize the durability of intervention effects.

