
### Eligibility criteria

Eligible participants are (1) consenting US. military veterans who are ≥ 19 years of age; (2) currently unemployed or underemployed (i.e., working < 20 h/week in competitive employment, or currently employed in a job that is not meaningful or well-matched to the veteran); (3) desiring to work in a competitive job; and (4) have a history of current or lifetime OUD according to DSM-5. Veterans with a history of traumatic brain injury may be included as long as they do not have a severe cognitive disorder. The key to attaining and sustaining employment in the context of a recovery model is being recognized for the potential contributions one has made in the past and can once again address moving forward. Eligible veterans are either unemployed, marginally employed, or caught in the trap of working in entry level jobs unrelated to their past education, training and/or military experience. The absence of work or career choices with relevance or meaning to the veteran’s life can be a determinant of accepting and sustaining treatment adherence. Meaningful work is often described as employment in a valued environment or performing work tasks related to one’s personal preferences or life experiences, military or non-military.

Exclusion criteria include (1) a current diagnosis of schizophrenia, schizoaffective disorder or other psychotic disorders; (2) diagnosis of dementia or severe cognitive disorder; (3) presence of current severe and unstable medical condition or terminal illness, that would contraindicate study participation or expose them to an undue risk; (4) unlikely that participant can complete the study, e.g., expected deployment, incarceration, long-term hospitalization, or relocation from the vicinity; (5) active suicidal or homicidal ideation making it unsafe for the participant to be included; or (6) current participation in another vocational interventional trial.

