### Employment outcome assessments

The primary outcome is the number of weeks worked during the 18-months following randomization. A “week worked” is defined as working either full- or part-time in a competitive job during a 7-day period. Competitive employment is defined as a job that pays at least minimum wage based on wages, salary, or commission, is in a setting not set aside for those with mental illness or disabilities, and is not transitional work. The exploratory employment outcome will be ‘steady worker’ status, defined as obtaining competitive employment for at least 50% of the active follow-up period (i.e. ≥ 32 weeks). Longitudinal employment data will include number of weeks, days, and hours worked in a competitive job, dollars earned, type of job(s), number of jobs, and job satisfaction. Job satisfaction is measured with the Indiana Job Satisfaction Scale (IJSS) [33]. Employment outcomes and IPS or non-IPS-VR services received will be collected using a calendar approach and verified by copies of pay documents (e.g., pay stub, direct deposit notices, pay checks).

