### MOUD outcome assessment

We are allowing Veterans on all types of MOUD (e.g., methadone, suboxone, naltrexone etc.) to be part of the study. We will ensure that type of MOUD will be controlled for in all statistical models at the end of the study. Adherence and relapse (i.e., opioid misuse ≥ 4 times/month) will be measured using the TAPS-2 Tool and pharmacy records. Adherence is defined as the number of days MOUD was received as indicated during the last 4 weeks of the intervention period.

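### The primary model leaves out whether a veteran already holds a competitive job at entry, and the article states its covariates in two ways: gender alone, or type of MOUD as well

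*Protocol article*

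**What the plan says.** All references are to the Protocol article.

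- **Primary model (Primary outcome analysis).** The fixed part is "study arm (IPS vs. non-IPS-VR) as the main independent variable adjusted for gender"; how time enters is decided after the data are plotted. The random part is also given: "Study site will be treated as a random effect, as will participant to account for the nesting of participants within sites".
- **Second covariate rule (MOUD outcome assessment).** "We will ensure that type of MOUD will be controlled for in all statistical models at the end of the study". The Primary outcome analysis section has no MOUD term and does not refer to this rule.
- **Who may enter (Eligibility criteria).** Underemployment is explained as "working < 20 h/week in competitive employment, or currently employed in a job that is not meaningful or well-matched to the veteran".
- **What counts (Employment outcome assessments; Primary outcome analysis).** "The primary outcome is the number of weeks worked during the 18-months following randomization", and "A week scored as “worked” is one in which a competitive job was held for any number of hours or days during that week". Neither section excludes a job already held at randomization.
- **What is balanced by design (Randomization and follow-up schedule).** Allocation is 1:1 and stratified by site only.
- **What is recorded at baseline.** Table 2 lists employment status: 4/25 underemployed in the IPS arm, 2/16 in the non-IPS-VR arm, 6/41 overall. Table 3 lists MOUD in the past 12 months: 12/25, 4/16 and 16/41.

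**The concern.** A participant who enters with a competitive job of a few hours a week, and simply keeps it, scores every week of follow-up (about 78) without any contribution from either service. Someone who enters unemployed starts scoring only once a job is found. Job-holding at entry should therefore be among the strongest predictors of the primary outcome. Yet the design does not balance it and the model does not adjust for it. The repeated-measures structure does not pick it up either, because cumulative weeks worked is zero for everyone at randomization.

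The MOUD rule raises a different problem. One section fixes the primary covariate as gender; another adds type of MOUD to every model. An analyst who follows either one departs from the other. The Secondary outcomes analysis section relies on all tests being pre-specified, so the primary model should not be open to two readings.

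**Working it through.** **1. The plan's own power figures.** With 54 per arm (60 × 0.90 = 54) and two-sided alpha 0.05 for a two-group comparison of means:

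- d = 0.55: 81.5% (normal approximation), 80.8% (t-test). The article states more than 81%.
- d = 0.54: 80.1% (normal), 79.4% (t-test). The article states 80%.

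The stated figures are reproduced. Nothing below says the sample size is wrong.

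**2. How many participants are concerned.** 6/41 = 14.6%, exact 95% CI 5.6% to 29.2%. Projected to 120 randomized: 120 × 0.146 ≈ 18. This is an upper figure for holding a competitive job at entry. Table 2 does not split underemployment by type, and the second eligibility route (a poorly matched job) does not say that the job is competitive.

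**3. Variance explained.** For a yes/no covariate with prevalence p and a gap of D weeks between holders and non-holders, R² = p(1 − p)D²/SD². The article gives neither D nor the outcome SD, so both are assumptions. With p = 6/41, p(1 − p) = 0.125:

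| SD (weeks) | D = 15 | D = 25 | D = 40 |
|---|---|---|---|
| 20 | 0.070 | 0.195 | 0.500 |
| 25 | 0.045 | 0.125 | 0.320 |
| 30 | 0.031 | 0.087 | 0.222 |

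If the gap equals one SD, R² is p(1 − p). Over the confidence limits for p this runs from 0.056 × 0.944 = 0.05 to 0.292 × 0.708 = 0.21. I therefore use 0.05 to 0.20 as the working range.

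**4. Gain from adjusting.** The residual SD shrinks by √(1 − R²), so the effective d is 0.54/√(1 − R²). With 54 per arm, t-test:

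| R² | Power at d = 0.54 | Detectable d at 80% power |
|---|---|---|
| 0 | 79.4% | 0.544 |
| 0.05 | 81.4% | 0.530 |
| 0.10 | 83.4% | 0.516 |
| 0.20 | 87.5% | 0.487 |

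This treats the primary test as a comparison of two means, as the article's own power statement does.

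**5. Chance imbalance.** The SD of the between-arm difference in prevalence is √(2 × 0.125/54) = 0.068. A one-SD imbalance moves the unadjusted contrast by 0.068 × D, which is 1.0 to 2.7 weeks for D = 15 to 40. The target effect is 0.54 × SD = 10.8 to 16.2 weeks for SD = 20 to 30. In standard-error units the shift is √R², so 0.22 to 0.45 standard errors for R² = 0.05 to 0.20.

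**6. The two covariate statements side by side.** The primary model has arm and gender as fixed terms, and site and participant as random terms. The MOUD rule covers every model, and the primary model is one of them. In Table 3, 41 − 16 = 25 of 41 (61%) had no MOUD in the past 12 months, so a type-of-MOUD covariate cannot be fitted to the whole sample without a none category. The article does not mention one.

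**The case against.** The strongest reply is that leaving out a prognostic covariate is not an error. Randomization makes the contrast unbiased in expectation, and the ordinary standard error already allows for chance imbalance. Underemployment is also similar by arm so far: 16.0% against 12.5%, Fisher p = 1.0. All of this stands. A reader might infer that the primary estimate is biased, and the documents do not support that. What remains is a precision gain from a variable already in hand, and its size rests on assumed values of D and SD.

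It is also fair to say that the model is not bare, since site and participant are in it, and that covariate detail often waits for the analysis plan. But the article does name its fixed covariates, and does so twice with different results. That is a conflict in the text and not an omission. The MOUD rule sits under the MOUD heading and may have been meant for those models only; its wording nevertheless reaches all of them.

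A reader might also infer that MOUD type is to be taken at study end, and so would be a post-randomization variable that IPS may affect. The text does not say this. The closing phrase of that sentence most naturally tells when the models are run, and OUD treatment is collected at baseline (Clinical assessments). The worry would apply only if a later measurement were used.

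Finally, the baseline tables might seem to call for adding SSI/SSDI status (20% against 50%), age or prior income. Arm differences seen at 41 of 120 participants are not a sound basis for choosing covariates. The income row is also unreliable, because its Total column repeats the non-IPS-VR column.

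**Conclusion.** The point holds as a matter of efficiency and of clear specification. Job-holding at entry is collected and plainly related to an outcome that counts weeks in that same job, but it is neither stratified nor adjusted for. Under an assumed R² of 0.05 to 0.20, adjustment would raise power at d = 0.54 from about 79% to between 81% and 88%. If fewer participants hold a competitive job than the 14.6% upper figure, the gain would be smaller for the same gap and SD.

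The conflict over type of MOUD needs no assumption: the two sections describe different primary models and must be reconciled. Neither part shows systematic bias or a wrong sample size.

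**What to change.** 1. State one covariate set for the primary model, all measured before randomization: gender, site (already present as a random effect) and holding a competitive job at baseline (yes/no). Use the competitive-job indicator in preference to the broader underemployed category.
2. Reconcile the MOUD outcome assessment and Primary outcome analysis sections. Either add type of MOUD as recorded at baseline, with a none level, or limit the MOUD rule to the aim 3 models.
3. Add a sensitivity analysis that counts only weeks in jobs started after randomization. It supports the primary analysis and does not replace it, because a veteran who keeps an entry job would score zero.
4. Do not add covariates on the strength of the interim differences between arms.

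The cost is a change of wording and one or a few degrees of freedom. Employment status and OUD treatment are already collected at baseline; the yes/no indicator may have to be derived from the recorded work history. The article reports no outcomes and 41 of 120 randomized, so the change can still be made as a genuine pre-specification.

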### Recruitment procedures

Participants are recruited from the Tuscaloosa VA Medical Center and the Birmingham VA Health Care System as they naturalistically present for treatment in vocational rehabilitation services, residential treatment program, outpatient mental health clinics, and addiction recovery programs, are referred to the study, respond to the IRB-approved advertisement/letter, or make personal inquiry into the study. During the 3-year enrollment period, we plan for at least 180 veterans to be directly offered consent, 140 to sign consent, 120 to be randomized, and 100 veterans to complete the study at the two sites. Participants are modestly compensated for each baseline and the bimonthly assessment visits.

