### Randomization and follow-up schedule

Participants who meet eligibility criteria are randomized (1:1) to either IPS or non-IPS-VR. Randomization uses a permuted block design of randomly varying block sizes stratified by site. Once assignment is made, the participant is analyzed in that group regardless of future events or services rendered, in accordance with the intent-to-treat principle.

Once informed consent is obtained, baseline assessments are administered. Participants are assessed at baseline and every 2 months (months 2, 4, 6, 8, 10, 12, 14, 16) and then final assessment at month 18 for employment outcomes and secondary outcomes. At each research visit, participants are assessed for the occurrence of adverse events or serious adverse events. The 18-month follow-up period allows for start-up time involved in each intervention prior to establishing competitive work and allows enough time for a participant to establish steady competitive work and achieve the secondary outcome goals.

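### Study site, the stratification factor with only two levels, is modelled as a random effect whose variance cannot be reliably estimated; a fixed two-level term should replace it

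*Protocol article*

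**What the plan says.** Recruitment procedures names both centres, "Participants are recruited from the Tuscaloosa VA Medical Center and the Birmingham VA Health Care System", and plans for "100 veterans to complete the study at the two sites". Study setting names the same two centres and no other. Under Randomization and follow-up schedule, "Randomization uses a permuted block design of randomly varying block sizes stratified by site"; no other stratification factor is named.

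Primary outcome analysis has "study arm (IPS vs. non-IPS-VR) as the main independent variable adjusted for gender". Site is not among these fixed terms. It enters as follows: "Study site will be treated as a random effect, as will participant to account for the nesting of participants within sites". The one fallback stated there concerns the covariance of the repeated outcomes, where the analysts "will proceed respectively to autoregressive and exchangeable structures if convergence issues are encountered". The arm difference is then taken from predicted marginal means, to "test significance at the *p* < 0.05 level".

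**The concern.** A random effect for site asks the model to estimate a variance from two realised values. That leaves 1 degree of freedom, and a variance estimated so poorly often lands on its boundary of zero. When it does, the fitted model is the same as one without site. The factor used to stratify randomization would then be adjusted for in some realisations of this trial and not in others, decided by the data and not by the plan.

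Two things are at stake. One is a primary model whose adjustment for the stratification factor is not guaranteed. The other is the standard error of each arm's own marginal mean, because the site variance enters it directly. This is a choice the article states outright, so it is not a detail left to an analysis plan that is not shown.

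**Working it through.** **Inputs.** Two sites (Recruitment procedures, Study setting). 120 randomized, 60 per arm, 54 per arm analysable, effect sizes 0.54 and 0.55 (Primary outcome analysis). Allocation so far 10 and 15 on IPS, 3 and 13 on control (Results). The article gives no between-site SD, so the values 0 to 0.5 outcome SDs below are assumptions. Two-sided testing at 0.05 is also assumed.

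**1. The plan's power.** Noncentrality = d × √(54/2).
- d = 0.55: 0.55 × 5.196 = 2.858. Power is 81.5% (normal) or 80.8% (noncentral t, 106 df).
- d = 0.54: 0.54 × 5.196 = 2.806. Power is 80.1% (normal) or 79.4% (noncentral t).

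The stated figures reproduce under the normal approximation.

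**2. Precision of a variance on 1 df.** Even with both site means known without error, the 95% interval is the estimate divided by the chi-square quantiles on 1 df.
- Lower multiplier: 1/χ²(0.975) = 0.20.
- Upper multiplier: 1/χ²(0.025) = 1018.
- On the SD scale: 0.45 to 31.9 times the estimate.

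**3. How often the estimate is zero.** With m per site and site SD s in outcome SDs, the REML-type estimate is zero when the site mean square is below the within-site mean square. The probability is P(χ²₁ < 1/(1 + m s²)). With m = 60:

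| Assumed site SD | 1/(1 + 60 s²) | P(zero), formula | P(zero), simulation |
|---|---|---|---|
| 0 | 1.000 | 68% | 67-70% |
| 0.1 | 0.625 | 57% | 57-59% |
| 0.2 | 0.294 | 41% | 42-46% |

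The simulation used 108 analysable participants, two sites split 50:50 or 32:68, 1,500 runs per scenario and a REML random site intercept. At a site SD of 0.5 it still gave zero in about 22% of runs.

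**4. Effect on the arm-level means.** Take one outcome per person, outcome SD 1, 54 per arm split evenly over the sites. The variance of one arm's mean is s²/2 + 1/54.
- s = 0.2: 0.0200 + 0.0185 = 0.0385, standard error 0.196.
- Site variance estimated at zero: 0.0185, standard error 0.136.

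**5. Effect on the arm difference.** In the same balanced case s² cancels: the variance is 2/54 and the standard error 0.192 whatever the site variance. The simulation fitted random-site and fixed-site models to the same data sets.
- Type I error: 4.7-6.0% under both. The Monte Carlo standard error is √(0.05 × 0.95/1500) = 0.6 points.
- Power at d = 0.55: 80.3-81.7% under both, differing by at most 0.2 points within any scenario.

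The simulation had arms balanced within site and one outcome per participant. It did not model the repeated cumulative-weeks outcome.

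**6. Cost of a fixed term.** With 105 instead of 106 df, noncentral-t power is 79.4% at d = 0.54 and 80.8% at d = 0.55, the same to the first decimal.

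**The case against.** The strongest reply is that nothing important changes. The only inference specified for the primary hypothesis is the arm difference in marginal means, a site intercept largely cancels from it, and step 5 shows no effect on error rate or power. That stands, within the limits of the simulation, and it keeps the point modest. It does not rescue the random effect, which gains nothing here and leaves adjustment for the stratification factor to chance.

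A reader might infer three stronger things that the article does not support.

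- *That a real site difference leaks materially into the arm effect.* Among the 41 participants randomized so far, 10/25 − 3/16 = 0.40 − 0.1875 = 0.21 more of the IPS arm is at site one, so dropping site with a 10-week site difference would seem to shift the contrast by about 2.1 weeks. But site is zeroed only when the observed difference is under about one standard error. With 60 per site, an observed 10 weeks would need an outcome SD above 10/√(2/60) = 54.8 weeks. An outcome bounded by 0 and about 78 weeks (18 × 52/12) has an SD of at most about 39. The imbalance also comes from 41 of 120 participants, and 1:1 blocks within site are meant to limit it by completion.
- *That a zero site variance triggers the fallback to autoregressive or exchangeable covariance.* A boundary estimate need not be a convergence failure, and the stated fallback concerns the repeated outcomes. The link is speculative.
- *That the variance cannot be estimated at all.* It can, on 1 df, but not usefully.

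**Conclusion.** The point holds as a fault in a stated modelling choice, of small to moderate weight. With two sites the between-site variance cannot be reliably estimated. Depending on assumed site SDs of 0 to 0.2, the stratification factor would in effect vanish from the fitted model in roughly 41% to 68% of trials of this size. Arm-level marginal means would carry unreliable standard errors. Type I error and power of the arm contrast are expected to be little affected; that expectation rests on a single-outcome, site-intercept simulation and has not been tested on the repeated cumulative outcome. The primary test is not broken and the sample size needs no revision. The case for change is that the better specification is almost free.

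**What to change.** In Primary outcome analysis, replace the random effect for site with a fixed two-level site covariate beside arm and gender, and keep the participant-level random effect or repeated-measures covariance. Carry the same term into the models that inherit this structure:

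- steady-worker status and the other employment outcomes described with the primary hypothesis;
- the psychological measures under Secondary outcomes analysis;
- the exploratory longitudinal models under MOUD analyses.

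The main adherence and relapse regressions under MOUD analyses state no site random effect, so there is nothing to replace in them.

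The cost is 1 degree of freedom and a change of wording. No data collection changes and the target of 120 stays. Enrollment and follow-up were still under way and no outcomes were reported in the article, so the change is best recorded before outcomes are examined by arm.
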